## Abstract

**Introduction:**

Blinding is a methodologically important aspect in randomised controlled trials yet frequently overlooked in trials of spinal manual therapy interventions for back pain. To help inform the blinding methods of a future, double-placebo-controlled trial comparing spinal manual therapy and nerve root injection for lumbosacral radicular pain, we set four objectives: (1) to assess the feasibility of blinding participants, randomly allocated to an active or placebo-control spinal manual therapy intervention protocol, (2) to assess the feasibility of blinding outcome assessors within the trial, (3) to explore the influence of spinal manual therapy experience and low back pain on blinding, and (4) to explore factors contributing to perceptions about intervention assignment among participants and outcome assessors.

**Methods and analysis:**

Two-parallel-group, single-centre, placebo-controlled, methodological blinding feasibility randomised trial. We will recruit between 60 and 100 adults with or without back pain and with or without experience of spinal manual therapy from Zurich, Switzerland. Participants will be randomised to either an active spinal manual therapy or a placebo-control spinal manual therapy protocol—both interventions delivered over two study visits, up to two weeks apart. The primary outcome is participant blinding using the Bang blinding index within each intervention arm immediately after each of the two study visits. Secondary outcomes are participant blinding using the James blinding index, outcome assessor blinding (Bang and James blinding indices), self-reported factors influencing perceived intervention assignment among participants and outcome assessors, and participant-reported credibility and expectancy of study interventions. Other outcomes—included to blind the study objective from participants—are lumbar spine range of motion, self-rated general health, satisfaction with care, pain intensity, and function. Intervention provider outcomes include intervention component fidelity and quality of intervention delivery.

**Ethics and dissemination:**

The independent ethics commission of Canton Zurich granted ethical approval for this study (KEK 2023–00381). Written informed consent will be obtained from all participants. Findings will be disseminated in scientific conferences and a peer-reviewed publication and inform the blinding methods of a future double-placebo controlled trial comparing spinal manual therapy and nerve root injection for lumbosacral radicular pain—the SALuBRITY trial.

**Trial registration:**

NCT05778396.

**Supplementary Information:**

The online version contains supplementary material available at 10.1186/s40814-024-01492-6.

## Introduction

Blinding—also called masking [1]—of interventions in randomised controlled trials (RCTs) mitigates biases that can threaten the internal validity of estimated treatment effects [2]. By withholding intervention assignment information from participants and outcome assessors, performance and detection biases can be minimised [3]. Successful blinding of participants may also foster retention and compliance with intervention protocols. To assess the success of blinding, participants, outcome assessors, and persons in other trial roles (i.e. intervention providers, data analysts, investigators) can be asked about their beliefs about intervention assignment. Blinding of participants throughout the study period can be an ambitious undertaking in RCTs of physical interventions, since participants may correctly identify (i.e., generate correct beliefs about) their treatment assignment [4]. In RCTs of spinal manual therapy (SMT), relatively little is known about the blinding status of participants and outcome assessors [5, 6].

Designing placebo-control interventions for SMT interventions, as well as other physical interventions, is inherently challenging [7]. Nevertheless, some attempts at placebo- or sham-control intervention design and assessment of blinding in RCTs of SMT have been made [8–12], with varying study populations, blinding assessment methods, and measurement timepoints. Studies that have asked about beliefs about intervention assignment and attempted to assess and report blinding success have not consistently relied on proposed blinding assessment statistical methods [13], which limit their interpretability and comparability.

Lack of information on blinding status of participants and outcome assessors and lack of formal blinding assessments in RCTs of SMT create a methodological gap, as suboptimal blinding may lead to biased treatment effect estimates [14], compromising the quality and interpretation of the evidence [15]. The quantitative assessment of blinding among participants and outcome assessors—although often overlooked—is an important and worthwhile methodological endeavour in RCTs of SMT interventions.

### Objectives

To inform the blinding methods of a future, double-placebo-controlled RCT comparing SMT and corticosteroid nerve root injection for the management of patients with lumbosacral radicular pain (i.e., spine-related leg pain)—the SALuBRITY randomised clinical trial (ISRCTN87156139)—we prespecify four objectives. First, we will assess the feasibility of blinding participants, with or without experience of SMT or current back pain, randomly allocated to either active or placebo-control SMT intervention protocols. Second, we will assess the feasibility of blinding outcome assessors—clinicians or clinicians in training that interact with participants and are responsible for assessing pre- and post-intervention session range of motion outcomes—within the RCT setting. Third, we will explore the influence of SMT experience in the past three months and the presence of low back pain during the past four weeks (3 or greater on a 0 to 10 numeric rating scale [NRS]) on participant and outcome assessor blinding. Fourth, we will explore factors contributing to participant and outcome assessor beliefs about assigned intervention using a qualitative thematic analysis.

## Methods

### Trial design and registration

Two-parallel-group (allocation ratio 1:1), single-centre, placebo-controlled, randomised blinding feasibility trial [16]. This trial protocol is reported in accordance with the SPIRIT 2013 guidance for protocols of clinical trials (Additional file 1) [17]. Our trial was preregistered on ClinicalTrials.gov: NCT05778396. Figure 1 details the trial design.

**Fig. 1 Fig1:**
[figure not shown]
Trial design

### Trial setting

Data will be collected, and interventions delivered at a community-based chiropractic research clinic in Zurich, Switzerland—CHIROMED Praxis im Seefeld ([name]). This research clinic actively collaborates and is affiliated with the EBPI-UWZH Musculoskeletal Epidemiology Research Group, within the Epidemiology, Biostatistics and Prevention Institute of the University of Zurich and the University Spine Centre Zurich of Balgrist University Hospital.

### Participants

#### Eligibility criteria

We will include participants aged 18 years or older with or without experience of SMT or current low back pain, to maximise recruitment feasibility of this study. Candidate participants—‘candidates’ hereafter—will be excluded if they have serious spinal pathology (e.g., spinal fracture, cancer or infection) or a history of lumbar spine surgery; are currently under care or in consultation with a specialist, chiropractor, physiotherapist, or osteopath for current low back pain; are a manual medicine health care provider (i.e., chiropractor, physiotherapist, osteopath, massage therapist, manual medicine trained physician); have a serious comorbidity preventing them from attending the research clinic and receiving the interventions; are pregnant or breastfeeding; are involved in pending litigation related to back pain; or are already participating in another research study related to back pain.

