### Randomisation

#### Allocation sequence generation

A computer-generated randomisation sequence will be generated by an independent statistician at the EBPI and used to randomly allocate participants to active or placebo-control SMT (1:1 ratio). Randomisation will be stratified by SMT experience as a patient or recipient in the past three months, and low back pain in the past four weeks (3 or greater on a 0 out of 10, NRS), and blocked with randomly varying block sizes, which will not be disclosed to ensure concealment of allocation of participants, outcome assessors, data analysts, and investigators.

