### Data collection and instruments

The inclusion and exclusion criteria (eligibility), patient information and informed expression of interest forms, will be completed online, prior to the first study visit. The informed consent form, study entry survey, and pre- and post-intervention assessments will be completed face to face. Trial coordinators will provide participants with a tablet or laptop with the REDCap survey [18] in the study clinic waiting area. Trial coordinators will have completed Good Clinical Practice (GCP) training prior to the start of the trial. The study entry survey includes questions on height, weight, gender, experience with SMT (in the past three months and lifetime), low back pain in the past four weeks, and average pain in the past four weeks. The following outcomes with their corresponding instruments will be captured:Range of motion of the lumbar spine: Measured by placing a measuring mobile phone at T12 with the participant standing, using the iOS application *Measure®* (iOS version 16.0.2, iPhone.® model X, Apple Inc., CA, USA) [31–33]Self-rated health: Measured with an item from the RAND 36-Item Short-Form Survey Instrument [34]Pain intensity: Measured with the NRS [35]Back function: Measured with selected items from the International Fitness Scale [36], the Cornell Musculoskeletal Discomfort Questionnaire [37], and a NRS (0 [Worst possible back function] to 10 [Best possible back function])Satisfaction with care: Measured by degree of agreement with the statement ‘I am satisfied with the treatment I received today’, with five Likert-type answers—‘Strongly agree’, ‘Agree’, ‘Uncertain’, Disagree’, and ‘Strongly disagree’Beliefs about intervention assignment: Measured with blinding questionnaires [13]—a standardised approach for blinding assessmentFactors influencing beliefs about intervention assignment: Assessed with the open-ended questions ‘Why do you believe you received this treatment?’ (participants) and ‘Why do you believe this participant received this treatment?’ (outcome assessors)Credibility/expectancy of interventions: Measured with the CEQ [28]Intervention fidelity: Assessed by asking intervention providers to record in case report forms information pertaining to participant tolerance, potential procedure alteration, and occurrence of joint cavitations immediately after intervention deliveryQuality of intervention delivery: Intervention provider-completed question ‘What number do you feel best describes the quality of the intervention delivery for this participant relative to the intervention protocol you were trained to deliver?’ with 11 possible answers on a 0 to 10 NRS

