### Statistical methods

Blinding analyses will be conducted using an intention-to-treat approach with the R package BI, version 1.1.0 [38, 39]. The current implementation of this package supports both Bang and James BI approaches, the presence of two intervention arms, and three intervention assignment beliefs by participants (i.e., ‘genuine’, ‘control’, and ‘do not know’). Information from the five-level blinding assessment items will be descriptively analysed and tabulated with numbers and percentages. To explore the influence of SMT experience on blinding feasibility of participants and outcome assessors, the responses from the blinding assessment will be described as counts and percentages, by levels of SMT experience. Within- and between-group changes in pain intensity and lumbar ROM will be described, although no formal statistical testing is performed given that these outcomes are collected to blind the study objective from participants and are not relevant to the blinding feasibility assessment. Factors contributing to perceptions about intervention arm assignment among participants and outcome assessors will be analysed using qualitative thematic analysis [27]. The analytical approach is informed by previous feasibility work [40]. Initially, three investigators (blinded to assigned interventions) will independently group similar responses using colour codes. Subsequently, they will develop themes through an iterative and consensus-based process.

To assess the impact of possible deviations from allocated intervention, an as-treated analysis accounting for potential lack of adherence or human errors by intervention providers will be conducted, if applicable and appropriate, to assess blinding outcomes.

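### Objective 3 names recent spinal manual therapy and recent low back pain, but the stated table is by manual therapy experience alone and cannot separate the two

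*Protocol article*

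**What the plan says.** The Objectives section sets out to "explore the influence of SMT experience in the past three months and the presence of low back pain during the past four weeks", with pain defined as 3 or more on a 0 to 10 scale, for participant and outcome assessor blinding alike. The Discussion repeats both factors.

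Both are built into the design. Under Allocation sequence generation, randomisation is "stratified by SMT experience as a patient or recipient in the past three months, and low back pain in the past four weeks". Under Data collection and instruments, the study entry survey records "experience with SMT (in the past three months and lifetime), low back pain in the past four weeks".

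Under Statistical methods, the analysis stated for this objective concerns SMT experience only: "the responses from the blinding assessment will be described as counts and percentages, by levels of SMT experience". No description by low back pain, and none by the two factors together, is given.

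Under Eligibility criteria, adults may enter "with or without experience of SMT or current low back pain, to maximise recruitment feasibility of this study", but candidates are excluded if they "are currently under care or in consultation with a specialist, chiropractor, physiotherapist, or osteopath for current low back pain". Under Recruitment, sampling is by convenience and purposive selection.

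**The concern.** An objective with two factors has a stated analysis with one. Half of the objective therefore has no stated description, and the other half is described in a way that cannot isolate it.

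A contrast between people with and without recent SMT reflects SMT alone only if the share with pain is the same in both groups, or if pain has no bearing on beliefs. The trial cannot assume the second, because the influence of pain is one of its own questions. It has no reason to expect the first: the sample is not random, and one exclusion acts on current care for back pain, which plausibly touches both factors. Stratified randomisation makes the arms alike within strata. It does not make recent SMT and pain independent of each other.

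At stake is an exploratory message about whether people with SMT experience are harder to blind. The results are meant to guide a later trial in patients with lumbosacral radicular pain, for whom the SMT contrast among people with pain is the closer one. A pooled table hides whether this sample can say anything about it.

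**Working it through.** **The plan's own figures.** The article gives no number for objective 3. Its sample size does reproduce. Thompson's worst case has three categories and constant 1.2736, so n = 1.2736 / 0.225² = 25.16, rounded up to 26 per arm. With 15% attrition this becomes 26 × 1.15 = 29.9, or 30 (26 / 0.85 = 30.6, or 31, by the other convention). Nothing in this point changes that figure.

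**Inputs.** From the article: 60 to 100 participants, 1:1 allocation, two binary strata. Everything else is assumed, because the article gives no prevalence of recent SMT or pain, no association between them and no exclusion rate:

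- p₁, p₀: share with pain among candidates with and without recent SMT, before exclusion
- x₁, x₀: share of those with pain whom the care exclusion removes
- D: difference in a response percentage between people with and without pain, 10 to 30 points
- true effect of SMT: none

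**Formulas.** After exclusion the pain share is A = p₁(1 − x₁) / [p₁(1 − x₁) + 1 − p₁] in the SMT group, and B likewise from p₀ and x₀ in the other. If people without pain respond at rate r, the groups show r + A·D and r + B·D. The one-way table then shows a false SMT difference of (A − B)·D.

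| p₁ / p₀ | x₁ / x₀ | A | B | A − B | False difference, D = 10 to 30 points |
|---|---|---|---|---|---|
| 30% / 30% | 0 / 0 | 30.0% | 30.0% | 0 | 0 |
| 30% / 30% | 80% / 10% | 7.9% | 27.8% | −19.9 | −2.0 to −6.0 |
| 50% / 30% | 0 / 0 | 50.0% | 30.0% | +20.0 | +2 to +6 |
| 50% / 30% | 57% / 0 | 30.1% | 30.0% | +0.1 | about 0 |
| 50% / 30% | 80% / 10% | 16.7% | 27.8% | −11.2 | −1.1 to −3.4 |
| 70% / 30% | 0 / 0 | 70.0% | 30.0% | +40.0 | +4 to +12 |
| 70% / 30% | 80% / 10% | 31.8% | 27.8% | +4.0 | +0.4 to +1.2 |

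Example, second row: 0.30 × 0.20 / (0.06 + 0.70) = 0.079 and 0.30 × 0.90 / (0.27 + 0.70) = 0.278. The gap of −0.199 times 0.10 to 0.30 gives −2.0 to −6.0 points.

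The largest value, +12, occurs with no exclusion at all. The exclusion can create the imbalance (row 2), cancel it (row 4 against row 3), reverse it (row 5) or shrink it (row 7 against row 6). If pain moved the response the other way, every sign would flip.

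**Within strata.** With no SMT effect, both SMT groups respond at r + D among people with pain and at r among people without. The SMT difference within each pain level is 0 in every row.

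**Cell size.** The SMT-with-pain cell holds N × (share with recent SMT) × (share of those with pain). With both shares assumed at 10% to 50%, this is 0.6 to 15 people at N = 60 and 1 to 25 at N = 100, both arms together, and about half that per arm.

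**The case against.** The strongest reply is that the objective is exploratory, the analysis is descriptive, and a condensed article may leave a cross-tabulation to the full protocol. The exploratory status stands and limits the consequence. Deferral to a fuller document is only a partial answer: the article does state an analysis for this objective, and it covers one of the two named factors. If the fuller document already has the joint table, one sentence settles the matter.

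A reader might infer something stronger: that the exclusion itself causes the mixing, leaves recent SMT users mostly free of pain, and so hides a true effect of experience. The article does not support this. The rule concerns current care for current low back pain, whereas the strata look back three months for SMT and four weeks for pain. People whose care has ended, or who had SMT for another complaint, remain eligible. The rule also covers specialist care, so it can remove people with pain and no recent SMT. It thins the cell without necessarily emptying it, and it can reduce an imbalance as well as create one.

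A reader might also put the effect on the Bang scale, for instance (0.10 − 0.50) × (0.50 − 0.10) = −0.16, and set it against the 0.3 adequacy limit. Those shares and index values have no basis in the article and assume the direction of the imbalance. The plan states counts and percentages here, and the 0.3 limit applies to whole arms.

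The objection to sparse data also stands in part. Bang indices in eight cells (four strata in two arms) from 60 to 100 people would be too imprecise to require.

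**Conclusion.** The point holds in a limited form. The stated analysis omits one of the two factors in objective 3, and the one-way SMT contrast it does state can carry a pain component. That component is of unknown size and sign. The illustrative range of about −6 to +12 percentage points rests wholly on assumed pain shares, exclusion rates and a positive pain effect of 10 to 30 points. The eligibility rule is one possible contributor and is not an error. An unknown sign does not rescue the one-way table, because a reader could not correct for the mixing without the joint counts. The primary outcome and the sample size are untouched. The change is worth making because it lets the trial address its own objective at almost no cost.

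**What to change.** Amend Statistical methods so that, within each arm, the belief responses of participants and outcome assessors are tabulated as counts and percentages by the four strata formed by recent SMT (yes/no) and recent low back pain (yes/no). This supplies the missing breakdown by pain. Read the SMT contrast within each pain level and the pain contrast within each SMT level, descriptively and with cell counts shown. If the cell with both recent SMT and pain is nearly empty, state that the SMT contrast does not extend to people with pain.

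Bang indices by cell, or standardisation to a common pain mix, are optional.

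The cost is one table from variables already recorded. Completed recruitment is no obstacle, since only the analysis changes. The downside is small cells, which the counts will make visible.

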### Recruitment, screening, and informed consent

Candidates will be recruited by convenience and purposive sampling via word of mouth, snowballing, and mass email advertisements through the University of Zurich and Balgrist University Hospital mailing lists. Candidates will be approached for interest directly by study team members in and around the Zurich area. Candidates that express preliminary interest will receive an invitation email with study details. Those expressing willingness to consider participation will be able to prebook their study visit appointments and will receive a REDCap study eligibility survey [18]. Eligible candidates will be directed to review the study participant information form and complete an electronic signature in REDCap to express interest and willingness to participate. Participants will be blinded to the study objectives as the study information and consent form state that the aim of the study is to find out whether two SMT interventions are ‘practical and acceptable’ for a future study in patients with back pain (Additional file 2). Active SMT is described in the study information and consent form as an ‘active or real treatment, with an unknown exact benefit’. Placebo-control SMT is described as ‘other manual therapy procedure that is a comparison or control treatment that is not known to have a benefit’.

At the first clinic appointment, the trial coordinator reviews the participant information form with the candidate, answers any questions, confirms candidate understanding and agreement to participate, and requests the candidate to sign the official study informed consent form. Candidates completing these steps are deemed enrolled study participants.

### Interventions

SMT is conceptualised as a pragmatic hands-on treatment directed towards the spine that includes manipulation, mobilisation, or both [15]. Spinal manipulation is manual therapy applied to the spine that involves a high velocity, low amplitude impulse, or thrust applied at or near the end of the passive range of motion of the spinal joints [19]. Spinal mobilisation is manual therapy involving passive movement applied to a spinal region or segment that incorporates movements within spinal passive range of motion with the aim of achieving a therapeutic effect [20]. Mobilisation includes spinal traction, which is application of an intermittent or continuous distractive force within the passive range of motion.

Up to 10 licensed Doctors of Chiropractic Medicine intervention providers (‘intervention providers’ hereafter) with at least three years of clinical experience will be trained in the delivery of active and placebo-control SMT interventions according to prespecified intervention descriptions and standard operating procedures (see Additional file 3A) for consistent study interactions with participants and high-fidelity intervention delivery.

Up to eight outcome assessors—clinicians or clinicians in training not delivering the interventions—will be trained in range of motion outcome assessment procedures. Outcome assessors will collect ROM measurements immediately before and after intervention sessions. During training, outcome assessors will gain competence in standardised ROM data collection and interactions with participants within the RCT setting (see Additional file 3A for details). Importantly, outcome assessors will be blinded to the complete study protocol and objectives and will be told that the aim of the study is to assess the feasibility of two SMT interventions and improve the quality of a future study.

Participants will receive two sessions of the assigned intervention, up to two weeks apart, to maximise retention and minimise the risk for missing data. Participants who are lost to follow-up after study visit 1 will be asked for reasons for discontinuation. Due to our blinding feasibility primary objective, concomitant care is not restricted outside of the trial.

